### Interventions

#### Intervention description {11a}

In the intervention group, patients will receive HFNC when they are awake in daytime and early evening hours. When they are asleep or at night between 10 pm and 6 am, these patients will change to NIV. The HFNC group will be given a flow rate of 60 L/min and a temperature of 37° C [17]. If a patient is not tolerating these settings, flow rate and temperature will be titrated to the maximum tolerated level, but with a minimum flow rate of 30 L/min.

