#### Criteria for discontinuing the trial {11b}

Participants are allowed to discontinue and end their participation in the trial at any time for any reason. Each patient’s attending physician will make the decision to cease HFNC or NIV at any time when encountering emergency circumstances and/or for any urgent medical reasons if the patient shows signs of worsening respiratory failure or if they show one or more of the following conditions: respiratory pauses, with a loss of consciousness defined as GCS score less than 8/15 [17], bradycardia (heart rate < 50 beats per minute (bpm)) and tachy-arrythmia (heart rate > 150 bpm) [20], hypotension with a blood pressure < 90/60 mmHg [11], psychomotor agitation making nursing care impossible or requiring sedation [2], and respiratory or cardiopulmonary arrest. If such conditions happen to the patient, they may need to be intubated either to protect the airway or to manage tracheal secretions and given mechanical ventilation as per usual practice. Finally, the trial will end if the patient or legal representative rescinds their informed consent.

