#### Provisions for post-trial care {30}

We expect that intervention-related severe adverse events in this trial will be unlikely because the use of HFNC and NIV are both ventilatory support in patients with respiratory failure in current practice and we will upgrade to NIV or intubation if necessary. Nevertheless, we plan to provide health care and waive the fees about ventilation for participants who may encounter trial procedure-related medical situations. Post-trial care will not be provided.

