#### Outcomes {12}

The primary endpoint is the mean difference in PaCO_2_ from baseline to 24 h after randomization. Secondary endpoints include the following: (1) the mean difference in PaCO_2_ from baseline to 6, 12, and 18 h after randomization; (2) dyspnea score at 6, 12, 18, and 24 h; (3) overall discomfort score related to the ventilatory strategy and proportion of patients showing poor tolerance to treatment at 24 h (e.g., complaining about noise, pressure, temperature, gastric distension, vomiting, or claustrophobia); (4) the proportion of patients who change treatment strategies (switch to the other ventilatory strategy or to no support); (5) rate of treatment failure, defined as the proportion of patients who had PaCO_2_ worsening or reduction < 10 mmHg from baseline, or worsening with no improvement of the dyspnea or respiratory rate > 30 breaths per minute; (6) respiratory rate; (7) rate of endotracheal intubation within 24 h; (8) length of hospital stay; and (9) all-cause mortality.

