### Data collection and measurement {18}

We will collect patient personal and baseline clinical characteristics as delineated above (e.g., age, gender, RASS, etc.). Furthermore, we will collect vital signs, systolic and diastolic pressure, heart rate, peripheral oxygen saturation, the presence of dyspnea based on the Borg dyspnea scale (score from 0 to 10 after 6 min’ walk, 0 means no dyspnea, 10 means the maximum), the arterial blood gas at inclusion, and starting time and settings for HFNC/NIV at 6, 12, 18, and 24 h. During the study intervention, patients will have continuous SpO_2_, electrocardiogram, respiratory rate, and noninvasive blood pressure monitoring. All relevant variables and endpoints will be evaluated at 6, 12, 18, and 24 h after randomization. In particular, we will record the NIV and HFNC settings as well as the proportion of patients who change treatment modality during the study period (i.e., switch to the other ventilatory strategy or to no ventilatory support). The discomfort score related to different ventilatory strategies will also be assessed at the established time points, and the proportion of patients showing poor tolerance to the treatment but who do not interrupt or withdrawal due to noise, temperature of flow, gastric distension, vomiting, or claustrophobia will be recorded. We will also record the rate of treatment failure due to a worsening PaCO_2_, a less than 10 mmHg reduction in PaCO_2_ from baseline, a worsening or lack of improvement in dyspnea, or a respiratory rate > 30 breaths per minute. Hospital length of stay and any-cause in-hospital mortality will all be collected. The main schedule of enrolment, intervention, and assessment were listed in the Table 1.

**Table 1 Tab1:** Schedule of enrolment, intervention, and assessment

Time point	Study period						
	Enrollment	Allocation	Post-allocation				
			Start	6 h	12 h	18 h	24 h
Enrollment							
Eligibility	** × **						
Informed consent	** × **						
Allocation		** × **					
Intervention							
Intervention group			** × **	** × **	** × **	** × **	** × **
Control group			** × **	** × **	** × **	** × **	** × **
Assessment							
Patient characteristics	** × **						
Vital signs	** × **		** × **	** × **	** × **	** × **	** × **
Medical history	** × **						
Laboratory results							
ABG			** × **	** × **	** × **	** × **	** × **
RASS score			** × **	** × **	** × **	** × **	** × **
Borg Dyspnea score			** × **				** × **
Discomfort score			** × **				** × **

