Secretions							
Treatment change							** × **
Treatment failure							** × **
Endotracheal intubation							** × **

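### The treatment-change endpoint pools a switch to the other strategy with a move to no support, so a difference (or equality) between arms on this secondary endpoint has no clear meaning

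*Protocol article*

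**What the plan says.** Outcomes {12} lists as secondary endpoint (4) "the proportion of patients who change treatment strategies (switch to the other ventilatory strategy or to no support". Data collection and measurement {18} gives the same definition: "the proportion of patients who change treatment modality during the study period (i.e., switch to the other ventilatory strategy or to no ventilatory support". Table 1 has one row, "Treatment change", marked at 24 h only.

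Neither definition separates the two destinations, asks for the reason for a change, or says which direction is favourable.

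Other parts of the protocol show why a patient's support may change:
- Provisions for post-trial care {30} foresees escalation: "we will upgrade to NIV or intubation if necessary".
- Criteria for discontinuing the trial {11b} lets the attending physician cease HFNC or NIV "if the patient shows signs of worsening respiratory failure or if they show one or more of the following conditions", and lets a participant leave at any time for any reason.
- Intervention description {11a} schedules one change by design: "When they are asleep or at night between 10 pm and 6 am, these patients will change to NIV".

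Statistical analysis {20} compares categorical variables between arms by a chi-squared or Fisher test. No separate rule is given for endpoint (4).

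**The concern.** A proportion used as a trial endpoint should have a direction: more of it is better, or more of it is worse. This one counts each of the following as a single event:
- an intervention patient moved to continuous NIV because blood gases worsen;
- a control patient moved to HFNC because the mask is not tolerated;
- a patient taken off support because the exacerbation has improved;
- a patient who declines all support but stays in the study.

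The third is a good outcome and the others are not. If one strategy allows earlier weaning, its benefit appears as more treatment changes. If one arm has more weaning and the other more switching, the two offset each other.

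This matters because better tolerance and fewer NIV failures are the rationale for the combined strategy (Background and rationale {6a} and Discussion), and a change of strategy is a natural place to look for them.

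**Working it through.** **Is there a plan figure to reproduce?** Not for this endpoint: the protocol gives no expected rate, component rate or power for treatment change. The only figure borrowed below is the arm size. Sample size calculation {14} states 58 in total, so 58 / 2 = 29 per arm. That total reproduces for the primary endpoint: with margin 5, SD 9, assumed means 54 and 55 mmHg and one-sided alpha 0.05, the distance to the margin is 5 + 1 = 6 mmHg, and a noncentral-t calculation gives power 0.806 at 29 per arm.

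**Does the same result carry opposite meanings?** Let R be the proportion moved to no support after improvement and F the proportion switched for worsening or intolerance, with no patient in both. Endpoint (4) then reports C = R + F. All rates below are assumptions for illustration.

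| Case | Arm A: R + F = C | Arm B: R + F = C | Reading of C |
|---|---|---|---|
| 1 | 30% + 10% = 40% | 10% + 10% = 20% | Arm A higher, and A is better |
| 2 | 10% + 30% = 40% | 10% + 10% = 20% | Arm A higher, and A is worse |
| 3 | 20% + 10% = 30% | 10% + 20% = 30% | No difference, although A is better on both parts |

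Cases 1 and 2 give the same C in each arm. No test applied to C can tell them apart.

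**The same in counts, 29 per arm (assumed).** Arm A: 6 off support after improvement and 2 switched, (6 + 2) / 29 = 27.6%. Arm B: 2 and 6, (2 + 6) / 29 = 27.6%. The pooled risk difference is 0. The switched proportions are 2/29 = 6.9% and 6/29 = 20.7%. Testing those alone gives Fisher p = 0.25 (uncorrected chi-squared p = 0.13), so at this sample size the gain from splitting is in interpretation, not in significance.

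**Do other endpoints supply the missing direction?**
- Endpoint (3), poor tolerance: Data collection {18} describes recording it in patients who do not interrupt or withdraw. On that wording, patients who stop because they cannot tolerate treatment are counted only in endpoint (4).
- Endpoint (5): "rate of treatment failure, defined as the proportion of patients who had PaCO_2_ worsening or reduction < 10 mmHg from baseline", with further dyspnea and respiratory-rate criteria. It does not use change of strategy.
- Endpoint (7) covers intubation only.

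None of them divides the treatment-change proportion by destination or reason.

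**The case against.** The strongest reply is that endpoint (4) is a neutral process measure. The protocol claims no favourable direction for it, and endpoints (3), (5) and (7) each have a clear bad direction. That holds for failure judged by blood gases and symptoms and for intubation. It holds less well for intolerance that leads to stopping, given how poor tolerance is to be recorded.

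A second reply is that the breakdown is detail for the case report form or analysis plan, neither of which is shown. This would be fair if the protocol were silent. Here it fixes the pooled definition in two places, and that definition is the problem.

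Three stronger readings are tempting, and the document does not support them.
- *A reader might infer that nothing in the data will tell the components apart.* HFNC and NIV settings are to be recorded, with evaluations at 6, 12, 18 and 24 h, so the destination should largely be recoverable. Participant retention and withdrawal has the reasons for dropouts documented in a standardized form. The gap is narrower: no stated reason for a change of support in a patient who stays in the study, and no split in the endpoint as defined.
- *A reader might infer that weaning will be frequent enough to mask a real difference.* No weaning rate is given. Entry requires PaCO2 of at least 55 mmHg, and the sample-size means are 54 and 55 mmHg, apparently at 24 h, so the average patient is still hypercapnic then. Some early recovery remains compatible with those figures, but its frequency is unknown. The offsetting counts above were chosen to offset.
- *A reader might infer that endpoint (4) should be replaced by one for failure or intolerance.* That would overlap endpoint (7) if it included intubation, and the tested outcome would then rest on reasons judged by unblinded staff. Counting destinations is more objective.

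**Conclusion.** The point stands in limited form. As defined in both places, endpoint (4) adds a switch to the other strategy to a move to no support, and the total has no interpretable direction. This follows from the definition alone. It needs only that some moves to no support follow improvement and some do not, which the protocol does not exclude.

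The size in practice cannot be stated, because the document gives no component rates; the illustrations show what is possible, not what is likely. One of nine listed secondary endpoints is affected. The primary endpoint, the 5 mmHg margin and the sample size do not depend on it, and nothing here supports a claim that the trial's main conclusion is at risk. It is a cheap improvement that makes a secondary result readable.

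**What to change.** Keep the data and change how the endpoint is stated:

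1. Report and compare two proportions: (a) unplanned switch to the other ventilatory strategy; (b) move to no support. Say that the scheduled HFNC-to-NIV changes in the intervention arm are not counted in (a), since otherwise the other strategy is unclear for that arm.
2. Record the reason for each change at the time: improvement, worsening, intolerance or refusal.
3. Tabulate (b) by reason, so that weaning for improvement is not counted with failure or intolerance.
4. Keep the raw total of changes as a descriptive count, and leave intubation in endpoint (7).
5. Use the same wording in Outcomes {12} and Data collection and measurement {18}.

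The cost is a reworded endpoint and one added reason item. The protocol describes no form completed at each change, so a place to record the reason may have to be added. The reason is assigned by unblinded staff and is open to judgement; the breakdown by reason should therefore be read alongside the destination counts. No treatment rule changes.

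### Treatment failure and poor tolerance are each defined in two different ways, and the plan does not say how scheduled NIV, intubation or early death are classed in the secondary endpoints

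*Protocol article*

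**What the plan says.** **Treatment failure.** Outcomes {12} counts a patient whose PaCO2 rises, or falls by less than 10 mmHg, "or worsening with no improvement of the dyspnea or respiratory rate" above 30 per minute. Data collection and measurement {18} uses the same PaCO2 and respiratory-rate limbs, but its remaining text is "a worsening or lack of improvement in dyspnea, or a respiratory rate > 30 breaths per minute". Intubation and death are in neither list. They are separate endpoints in Outcomes {12}, the former as "rate of endotracheal intubation within 24 h".

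**Poor tolerance.** Outcomes {12} takes the proportion of patients with poor tolerance at 24 h and sets no further condition. Data collection {18} records "the proportion of patients showing poor tolerance to the treatment but who do not interrupt or withdrawal due to noise, temperature of flow" and further complaints.

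**Treatment change.** Outcomes {12} speaks of changing strategies and Data collection {18} of "the proportion of patients who change treatment modality during the study period". Both explain this as moving to the other ventilatory strategy or to no support. Intervention description {11a} gives the intervention arm HFNC while awake by day; when asleep, or between 10 pm and 6 am, "these patients will change to NIV".

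**Related rules.** Methods {20c} specifies complete-case analysis, with worst-case imputation as a sensitivity analysis. The trial is unblinded (Blinding {17}).

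**The concern.** Where an endpoint has two definitions, the same patient can be an event under one and not under the other. In an unblinded trial, that leaves the choice of definition open until results by arm are known.

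For tolerance, the direction of the problem is predictable. Removing patients who interrupt or withdraw makes an arm look better tolerated the more of its patients stop. The Discussion gives comfort and tolerance as a main reason for the new strategy, so this endpoint will be read closely.

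The two silent points have a similar effect. If scheduled night NIV is counted, the treatment-change endpoint measures the protocol and not the patients' course. If intubation and early death are not placed, a patient with one of the worst outcomes may not appear as a treatment failure.

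**Working it through.** **Denominator.** The plan gives no sample size for these endpoints, so the evaluable number for the primary endpoint is used. Sample size calculation {14} has margin 5 mmHg, means 54 and 55 mmHg (intervention better by 1), SD 9, one-sided alpha 0.05 and power 0.80. The normal approximation gives n per arm = 2 × (1.645 + 0.842)² × 9² / (5 + 1)² = 27.8, so 28 per arm and 56 in total. The noncentral t calculation gives power 0.793 at 28 and 0.806 at 29 per arm, so 29 per arm and 58 in total, as stated. One patient is 1/29 = 3.4 percentage points of an arm, or 1/33 = 3.0 with the abstract's total of 66.

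**Treatment failure: dyspnea limb.**

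| Dyspnea against baseline | Outcomes {12}, literal | Data collection {18} |
|---|---|---|
| Worse | failure | failure |
| Unchanged | not a failure on this limb | failure |
| Better | not a failure on this limb | not a failure on this limb |

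Only the middle row differs. The documents give no rate for it. Assuming 10%, 20% or 30%, the number affected is 58 × 0.10 = 5.8, 58 × 0.20 = 11.6 or 58 × 0.30 = 17.4, so about 6, 12 or 17. These are upper limits, because some of these patients fail on PaCO2 or respiratory rate anyway.

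**Poor tolerance.** In an arm of 29, let m patients tolerate treatment poorly but continue, and let s stop because of intolerance. Outcomes {12} gives (m + s)/29. Data collection {18} gives m/29 if those who stop stay in the denominator. The difference is s/29, or 3.4 points per patient who stops. If m is equal in the two arms and s is not, the second rule hides the whole difference, in favour of the arm with more stopping.

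**Treatment change.** A 24 h window from any start time covers each clock hour once, so it always contains 8 h of the 10 pm to 6 am period. Every intervention patient still on protocol at 24 h has therefore had a scheduled change of device. Counted by device, the rate is about 29/29. Against an assumed 0 to 9 switches among 29 controls, Fisher's exact p is below 1e-7, a difference produced by the schedule alone.

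**Intubation.** An intubated patient is a non-failure only if no limb is met. Mechanical ventilation can bring PaCO2 down by 10 mmHg or more and the respiratory rate to 30 or below. Data collection {18} scores Borg dyspnea after a six-minute walk, which an intubated patient cannot do, so that limb is likely to be missing. Such a patient is then either scored a non-failure on the two available limbs or lost from the complete-case analysis. If 5% to 15% are intubated (assumed), 29 × 0.05 = 1.5 to 29 × 0.15 = 4.4, so about 1 to 4 patients per arm are open to this.

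**The case against.** The strongest reply is that most of this is loose drafting. The dyspnea clause in Outcomes {12} is redundant as written, since worsening already excludes improvement, so it is probably a slip for the clause in Data collection {18}. That is plausible, but the Outcomes section is where a reader looks for the definition, and its literal meaning differs.

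Four stronger readings are tempting, and the documents do not support them.

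- *The two sections contradict each other on treatment change.* They do not: both give essentially the same explanation. The Abstract and Discussion also treat HFNC with sequential NIV as one strategy, and on that usage night NIV is no switch. What remains is an ambiguity, because the word modality invites counting by device and nothing excludes the scheduled change.
- *Patients who stop from intolerance are counted nowhere.* This is true only of the tolerance rule in Data collection {18}. Outcomes {12} does not exclude them, those who switch or go to no support enter the treatment-change endpoint, and reasons for dropout are documented.
- *Intubated patients are scored as successes.* Both definitions leave intubation out, so there is no conflict, and it is reported separately. A patient deteriorating towards intubation may also have met a limb at an earlier assessment: the text has endpoints evaluated at 6, 12, 18 and 24 h, while Table 1 marks failure at 24 h only, so it is unclear whether failure is cumulative. The worst-case sensitivity analysis may also recover patients with missing data. The gap is that the classification is not stated.
- *The complaint lists conflict because only one names pressure.* The list in Outcomes {12} is given as examples, so a shorter list elsewhere is no contradiction.

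The 10 mmHg PaCO2 threshold is the same in both sections and is not in dispute.

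**Conclusion.** The point holds as two direct conflicts and two unstated classifications, all in secondary endpoints. The conflicts are the dyspnea limb of treatment failure and the restriction on who counts as poorly tolerant. The first could move up to about 6 to 17 of 58 patients, if 10% to 30% have unchanged dyspnea. The second moves an arm's rate by 3.4 points for each patient who stops, and its bias depends on stopping rates differing between arms, for which the documents give no figures.

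The unstated classifications are scheduled NIV, where counting by device gives about 100% in the intervention arm by design, and intubation or death before 24 h. The estimate of about 1 to 4 intubated patients per arm at risk of being misplaced rests on an assumed rate of 5% to 15%, and misplacement also requires the other limbs to be unmet or missing.

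The primary PaCO2 endpoint and the sample size of 58 are not affected.

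**What to change.** Reconcile Outcomes {12} and Data collection {18}, before the data are analysed, so that each endpoint has one definition:

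- **Treatment failure:** use one dyspnea clause in both sections, stating whether unchanged dyspnea counts. For analysis, count patients intubated or dead by 24 h as failures, and continue to report intubation and mortality separately.
- **Poor tolerance:** count over all randomised patients, including those who stop because of intolerance.
- **Treatment change:** count unscheduled changes only, and say that the scheduled sleep or night NIV of the intervention arm is not a change.

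The cost is a few lines of text. Intubation, mortality, treatment changes, device settings and reasons for dropout are already to be collected. At most, the case report form needs a mark for whether a change was scheduled and the time of any death. Treatment of patients and the sample size stay as they are.

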#### Sample size calculation {14}

Based on previous studies [21], we set the non-inferiority cutoff at 5 mmHg. So, we assume that in the intervention group, PaCO_2_ may not elevate more than 5 mmHg after 24 h of the high-flow nasal cannula therapy with sequential noninvasive ventilation. According to previous studies, we also assume that the PaCO_2_ of intervention group is around 54 mmHg, and the control group is around 55 mmHg. Standard deviation is 9 mmHg, after 1:1 ratio randomization, and to assess non-inferiority using an *α* = 0.05, power = 0.80, and 1-side testing, 58 subjects were needed totally. Allowing for 10% loss to follow-up, we assume that we will need to recruit 70 patients. However, if loss to follow-up is greater than 10%, we aim to continue recruitment until 58 patients have a primary outcome recorded.

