**Methods:**

This investigator-initiated, unblinded, single center, randomized controlled trial will be conducted in the emergency department, emergency intensive care unit, or respiratory intensive care unit of a tertiary-care urban teaching hospital. A total of 66 patients will be enrolled and randomized into the intervention group (HFNC with sequential NIV) or the control group (NIV group). The primary endpoint will be the mean difference in PaCO_2_ from baseline to 24 h after randomization. Secondary endpoints include the mean difference in PaCO_2_ from baseline to 6, 12, and 18 h, as well as the dyspnea score, overall discomfort score, rate of treatment failure, respiratory rate, rate of endotracheal intubation, length of hospital stay, and mortality.

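### The planned number to recruit is given as both 66 and 70, and 70 does not follow from 58 evaluable patients with 10% loss

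*Protocol article*

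**What the plan says.** Three statements in the protocol article bear on the number to recruit.

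- **Abstract, Methods:** "A total of 66 patients will be enrolled and randomized".
- **Sample size calculation {14}, evaluable number:** "58 subjects were needed totally". The inputs are one-sided alpha 0.05, power 0.80, a standard deviation of 9 mmHg and 1:1 allocation, with "we set the non-inferiority cutoff at 5 mmHg" and the assumption that "the PaCO_2_ of intervention group is around 54 mmHg, and the control group is around 55 mmHg".
- **Sample size calculation {14}, number to recruit:** "Allowing for 10% loss to follow-up, we assume that we will need to recruit 70 patients".

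The same section adds a contingency. If loss turns out to exceed 10%, "we aim to continue recruitment until 58 patients have a primary outcome recorded". This last rule is conditional on the loss rate.

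The article gives no reason for 70 other than the 10% allowance, and it does not explain why the abstract differs.

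**The concern.** The abstract and the sample size section describe the same trial, so one of the two totals must be wrong or must rest on an allowance that is not stated. The total in the sample size section is also the one that the section's own inputs fail to produce.

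What is at stake is a stated design figure. The number to be randomised sets how long the allocation sequence must be and how many sealed envelopes are prepared, and it is the figure against which the final report will be compared. As written, stopping at 66 and stopping at 70 could each be described as following the protocol. The contingency is tied to a 10% loss rate, which suits a total of about 66 but not a total of 70.

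**Working it through.** **Inputs.** All come from Sample size calculation {14}, except the 66, which is in the abstract: margin 5 mmHg; assumed PaCO2 of 54 (intervention) and 55 (control), a true difference of −1 mmHg; SD 9 mmHg; one-sided alpha 0.05; power 0.80; 1:1 allocation; 58 evaluable; 10% loss; 70 to recruit.

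**Step 1: reproduce the 58.** The distance between the assumed difference and the margin is 5 − (−1) = 6 mmHg.

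- Normal approximation: n per arm = 2 × (9/6)² × (1.645 + 0.842)² = 27.8, so 28 per arm and 56 in total.
- Noncentral t: 29 per arm and 58 in total, with power 80.6%.

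The stated 58 reproduces exactly by the t-based calculation. The base figure is not in question.

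**Step 2: apply the stated 10% loss.**

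| Method | Calculation | Number to recruit |
|---|---|---|
| Divide by the proportion retained | 58/0.90 = 64.4 | 65 |
| Same, rounded up within each arm | 29/0.90 = 32.2, so 33 per arm | 66 |
| Multiply by 1.10 (a cruder variant) | 58 × 1.10 = 63.8 | 64 |

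None gives 70; the gap is 4 to 6 patients. The second row gives the abstract's 66.

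**Step 3: what loss would give 70?**

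- The largest loss at which 70 still leaves 58 is 1 − 58/70 = 17.1%.
- Rounding within arms, 35 per arm is the result for any allowance above 1 − 29/34 = 14.7% and up to 1 − 29/35 = 17.1%. For example, 29/0.85 = 34.1, so 35 per arm.
- By simple multiplication, 58 × 1.2 = 69.6, so 70 needs an allowance of about 20%.

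The allowance behind 70 is therefore roughly 15% to 20%, depending on the method. It is not 10%.

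**Step 4: what each total leaves.**

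| Recruited | Evaluable at 10% loss | Largest loss that still leaves 58 |
|---|---|---|
| 66 | 66 × 0.90 = 59.4 | 1 − 58/66 = 12.1% |
| 70 | 70 × 0.90 = 63.0 | 1 − 58/70 = 17.1% |

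**Step 5: check the contingency against each total.** With 66 recruited, the 10% trigger lies close to the 12.1% at which the evaluable number reaches 58, so the rule fits. With 70 recruited, a loss between 10% and 17.1% meets the rule's condition although 58 outcomes are already in hand. The rule then asks for nothing further, so it does no harm, but its trigger does not match the total.

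**The case against.** The strongest reply is that nothing of substance depends on the discrepancy. Both totals exceed 64.4, and both leave at least 58 evaluable at the stated loss. The departure to 70 errs on the safe side, and the margin, alpha, endpoint and analysis are untouched. The 70 may simply be 66 rounded up, since the article never mentions 17%. All of this stands, and it limits the severity. It does not remove the point: two totals remain in print, and the sentence containing 70 offers the 10% allowance as its only reason.

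Two stronger readings are tempting, and the document does not support either.

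- A reader might take the 58-outcome rule as a third, competing recruitment target. It is not one. It applies only if loss exceeds 10%, and it protects the evaluable number under either total.
- A reader might infer that two totals in an unblinded, single-centre trial invite stopping on a favourable result, and that the number randomised should therefore be made the fixed end of recruitment. The rule depends on how many primary outcomes have been recorded, not on their values, and the article describes no interim comparison of the arms tied to recruitment. No route to bias or an inflated type I error is shown. Fixing the total would also remove a safeguard: at 66 with 15% loss, 66 × 0.85 = 56.1, so only about 56 would be evaluable.

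**Conclusion.** The point holds as a correction of a stated design figure, of modest severity. The article gives the planned number as 66 in one place and 70 in another, a difference of 4 patients (4/66 = 6%). The 70 does not follow from 58 evaluable patients with 10% loss under any of the three inflation methods tried, while 66 does, with equal arms. Power is not lost under either total if loss is 10% as assumed.

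This conclusion takes the 58 as given; it reproduces on the stated inputs, and whether those inputs are well chosen is a separate matter. It does not settle which total was approved, because the article does not say. Nor does it establish that 17% was ever intended: that figure is a back-calculation from 70.

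**What to change.** State one planned number in both the abstract and Sample size calculation {14}. There are two routes.

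1. **If 66 is the planned number:** replace 70 in the sample size section with 66 (33 per arm), derived as 29/0.90 = 32.2, rounded up within each arm. The 10% trigger in the contingency can stay as it is.
2. **If 70 was approved:** change the abstract to 70 and state what produces it, either an allowance (up to about 17% loss) or an explicit rounding up from 66. Then align the contingency's 10% trigger with the restated allowance.

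Under either route, keep the rule of continuing until 58 primary outcomes are recorded.

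The cost is a change of wording in one or two places. It adds no patients to the approved total and does not touch the design or the analysis. If an allocation list and envelopes have already been prepared, their number should be checked against the total chosen.
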